#### Participants

Seventy-two (*N* = 24 per condition) infants from the Chicago area will be recruited from the laboratory database. Infants will have no more than 15% exposure languages other than English. Caregivers will complete a MacArthur Short Form Vocabulary Checklist: Level II [Form A; 32], augmented with words used in the experiments but not included in the form (see S1 Appendix). They will also complete a demographic questionnaire about their education, employment, gender, and race (see S2 Appendix).

The number of participants was determined based on power analysis performed with G*Power 3.1 [33] for a repeated measures between-subject F-test with target effect size *f*^2^ = .1225 (medium; [34], *alpha* = .05, power = .8, number of groups (experimental conditions) = 3, number of trials = 4, and projected correlation between measurements = .5. We reasoned that compelling evidence would require at least a medium effect size of experimental condition. Based on these parameters, the required number of participants is 72. The planned analyses include Generalized Linear Mixed Model rather than an F-test. We used F-test-based effect size estimations for simplicity. The four test trials were treated as repeated measures.

Participants may be excluded and replaced due to fussiness, crying, or equipment failure. Further, because our Covid-19 Contingency Plan (see below) involves testing infants using Lookit–an online platform designed for developmental research–we expect a data loss rate of about 47–50% [35] due to infants’ crying or fussiness, parental interference, or technological issues. This, we anticipate that the total number of infants recruited could reach 140.

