For each trial of each infant, we will calculate the proportion of looking time devoted to the target [looking to target/(looking to target + distractor)] throughout the analysis window. This should yield up to 4 data points for each infant (one per each of 4 trials). To assess the time course of infants’ attention to the animal and artefact images, eyetracker data will be aggregated by condition into a series of 100-ms bins. For data collected on Lookit, we will use 200-ms bins. Web-cameras typically have sampling rates varying between 30HZ and 60HZ, which translates to frame duration ranging from 16.67 ms to 33.33 ms. Binning our data into 200-ms segments allows us to have at least 6 frames in each bin and to calculate the proportion of infants’ looking to the target image. Fewer frames per bin would result in substantially cruder estimations of infants’ proportion of looking to the target.

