#### Analyses

The *dependent variables* (DVs) will be [1] infants’ proportion of looking time (LT) to the target image from the image display onset until 6 s later, averaged across four trials; [2] the time course of the proportion of LT for each 100-ms (or 200-ms) bin in the 6-s window. Because our goal is to evaluate the effect of semantic priming on infants’ word learning under the conditions of displaced reference, we will use Condition as the main *independent variable* (IV).

In analyzing the overall proportion of LT to the target, we will use a Generalized Linear Mixed Model (GLMM) with Condition as a fixed factor and Participant and Test Item as a random factors. We include the Test Item variable to account for the potential effects of infants’ knowledge in different domains–fruits, vehicles, clothing, and animals. We plan to use an identity link, which will require that we test the distribution of the data for normality. We will implement this by running a Shapiro-Wilk test. If the distribution of our data significantly deviates from normal, an appropriate transformation will be applied. In analyzing the time course, we will use the cluster-based permutation analysis [40] to identify significant divergences between the conditions that correspond to mention of the target word.

The effects of demographic factors, vocabulary scores, and trial order will be tested in a preliminary analysis, implemented by fitting a GLMM to the DVs. Trial order is included to test whether infants’ looking preferences change over the duration of the procedure, as they might lose interest or exhibit a learning effect as the experiment progresses. Only the factors that produce significant effects in the preliminary analysis will be included in the main analyses. No other analyses are planned for the data collected via the demographic survey.

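### The covariate set and, for the overall looking proportion, the outcome scale are left to significance tests on the study's own outcome data

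*Protocol article*

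**What the plan says.** All of this is in the Protocol article, mainly Experiment 1, Analyses.

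- **Fixed core.** The overall proportion of looking to the target is analysed with a "Generalized Linear Mixed Model (GLMM) with Condition as a fixed factor and Participant and Test Item as a random factors". An identity link is planned.
- **Covariates.** "The effects of demographic factors, vocabulary scores, and trial order will be tested in a preliminary analysis, implemented by fitting a GLMM to the DVs". The selection rule follows: "Only the factors that produce significant effects in the preliminary analysis will be included in the main analyses". The section gives no threshold and does not say whether Condition is in the preliminary model. Participants lists the questionnaire content: "They will also complete a demographic questionnaire about their education, employment, gender, and race".
- **Scale.** "We plan to use an identity link, which will require that we test the distribution of the data for normality". Then: "We will implement this by running a Shapiro-Wilk test". And: "If the distribution of our data significantly deviates from normal, an appropriate transformation will be applied". No transformation is named and residuals are not mentioned.
- **Unit.** Data preparation gives up to four values per infant ("For each trial of each infant, we will calculate the proportion of looking time devoted to the target"), whereas Analyses defines the first dependent variable as an average over the four trials.
- **Carry-over.** Experiment 2, Participants, adopts the same analyses and adds the looking score from the familiar-word test to the main analyses, with no screen.

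**The concern.** A registered report exists to fix the analysis before the outcome is seen. Here two parts of it depend on that outcome.

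First, covariates earn their place by being significant on the dependent variables. Noise factors can enter by chance and a useful covariate can be dropped. The adjusted model can differ between the two dependent variables and between the two experiments.

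Second, the normality rule looks at the wrong object. An identity-link Gaussian model needs roughly normal residuals. Data pooled over conditions with different means form a mixture, so the effect under test can itself help to trigger a change of scale. So can the 0-1 bounds on a proportion. The predictions are written in percentage points and tested against 50%. Once the data are transformed, that comparison has no stated equivalent: the mean of transformed proportions is generally not the transform of the mean proportion.

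**Working it through.** The plan states no figure on this point, so there is none to reproduce. The checks use its N of 72 (24 per condition), four trials per infant and projected correlation of .5 (Participants), and the pilot mean of 64% with SD 8 (Pilot data). The screening threshold, the number of terms and the trial-level SDs are assumptions.

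**1. Noise factors entering.** Education, employment, gender, race, vocabulary and trial order make six candidates if each is one term. With a .05 screen and all null, P(at least one enters) = 1 − .95^k:

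| Candidates k | P(at least one enters) |
|---|---|
| 4 | 18.5% |
| 6 | 26.5% |
| 8 | 33.7% |

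**2. A useful covariate being dropped.** For a vocabulary score correlated .3 with looking, Fisher's z gives atanh(.3) × √(72 − 3) = 2.57. Power at two-sided .05 is Φ(2.57 − 1.96) = .73, so the score is missed in about 27% of experiments by a simple correlation test. Simulation with the other candidates in the model, with and without a Condition effect, gives about 30-37%.

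**3. Type I error of the Condition test after screening** (simulated, 72 infants, six candidates, nominal .05):

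| Condition in the screening model? | Covariates explain nothing | Covariates explain 20% |
|---|---|---|
| No | .050 | .049 |
| Yes | .056 | .071 |

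**4. Power.** With a Condition effect of .8 SD, always adjusting against screening gives 83.5% against 81.7% at r = .3 (1.8 points) and 85.6% against 84.0% at r = .4 (1.6 points). At the pilot effect, 14 points over an SD of 8, or 1.75 SD, power is above .99 even unadjusted and the loss vanishes.

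**5. How often the scale switches.** Simulated Shapiro-Wilk rejection rates depend heavily on the inputs:

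| Values tested | Assumptions | Rejected |
|---|---|---|
| 288 trial values | clipped normal, moderate trial SDs | about 5% |
| 288 trial values | clipped normal, within-infant SD 20 points, pilot effect | 19-50% raw; 8-12% on residuals |
| 288 trial values | beta, within-infant SD 11 / 15 / 20 / 25 points, no Condition effect | 10 / 32 / 98 / 100% |
| 288 trial values | beta, pilot effect, correlation .5, infant-mean SD 8 or 10.8 | 21% or 16% |
| 72 infant means | various | about 3-9% |

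The second row shows that a true Condition effect contributes to the trigger.

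**6. Consequence of switching.** One transformation named in advance keeps type I error at .048-.051. Taking the best of raw, arcsine and logit after a rejection raises it to at most .059.

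**The case against.** The strongest reply is that little is at stake. The core model is written down, type I error is close to nominal and the power loss is under 2 points. Naming a transformation is the kind of detail that an article may leave to an analysis plan. Most of this stands, and it limits the point in four ways.

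- A reader might infer that the whole confirmatory model is unknown until the data are in. The document does not support that: Condition, Participant, Test Item and the identity link are stated.
- A reader might infer that the scale is open for both dependent variables. The normality rule belongs to the mixed model for the overall proportion. The time course is analysed by cluster-based permutation, and nothing ties the rule to it.
- A reader might infer that the transformation will almost always be triggered. Rates near 100% need trial-level testing and trial SDs of 20 points or more under a beta model. With the plan's correlation of .5, a total trial SD of 20 implies an infant-mean SD of 20 × √((1 + 3 × .5)/4) = 15.8, about twice the pilot's 8.
- Dropping trial order costs almost no precision. Every infant is scheduled for all four trials, so trial order is balanced across Condition. Only excluded trials could disturb this.

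The appeal to an unseen analysis plan does not remove the point. The article does not merely omit a detail: it states two rules that choose covariates and scale from the outcome.

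**Conclusion.** The point holds as a pre-specification weakness of moderate importance. For both experiments, the covariate set, and for the overall looking proportion the scale, depend on significance tests of the outcome. The normality test is aimed at the data and not at residuals.

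The size is modest. At least one null factor enters in about 26% of experiments, and a vocabulary score correlated .3 with looking is lost in about 30-37%. Type I error is about 5%, or 5-7% if Condition is in the screening model, and the power loss is at most about 2 points. These figures assume a .05 screen and infant-level linear models; the 26% also assumes six one-term candidates. How often the scale would switch cannot be fixed from the document, because it turns on the trial-level SD and on whether trial values or infant means are tested.

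A claim of serious false-positive inflation would go beyond the evidence. The main cost is that the covariates and the scale of the estimate, including its comparison with 50%, are not settled in advance, together with some precision from vocabulary.

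**What to change.** - Replace the screen with a fixed set, for example Condition plus vocabulary score, with Participant and Test Item kept as random factors. Trial order is optional, since it adds little to the precision of Condition.
- Use the same set in both experiments, plus the familiar-word looking score that Experiment 2 already adds. Report demographics descriptively.
- Delete the Shapiro-Wilk trigger. Keep the untransformed percentage-point model as primary, so that the 50% comparison stays as predicted, and check the model residuals.
- Name one sensitivity scale in advance, for example the empirical logit, where 0 corresponds to 50%. A plain logit is undefined at 0 and 1.
- Leave the cluster-based permutation analysis of the time course without outcome-selected covariates.

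The cost is wording, plus a few degrees of freedom for covariates that may prove unrelated: one for vocabulary and, if trial order is kept as a four-level factor, three more. The change needs to be made before the outcome data are seen, because afterwards it cannot be repaired credibly.

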#### Predictions

Because infants as young as 12 months infer the presence of a hidden object by following a speaker’s line of regard [41], understand that words communicate about mental states [42–44], and appreciate referential cues [5], we make the following predictions.

#### Proportion of LT to the target

Semantic Priming condition: We predict significant effects of Condition, with average proportion of LT (across 6 s) to the target significantly higher in the Semantic Priming than in the No Priming and Follow-up Control conditions. Further, we predict that if infants successfully infer the meaning of the novel word and establish a representation of its referent in the Semantic Priming condition, their LT to the target will be significantly above chance (50%).

No Priming condition: If infants’ looking behavior is influenced by semantic inferences, rather than baseline preferences, then their LT to both objects in the No Priming condition will be equivalent and will not deviate significantly from chance. We predict this because there is no basis for infants to infer the meaning of the novel word after being presented with three semantically distant word-object pairs.

Follow-up Control condition: If infants’ looking preference in the Semantic Priming condition is the result of the semantic relations among the objects themselves, then their performance in the Follow-up Control condition will not differ from the Semantic Priming condition. Conversely, if infants’ looking in the Semantic Priming condition reflects infants’ inferences about novel word meanings, their LT in the Follow-up Control condition should not significantly deviate from chance.

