**Fig 2 pone.0244968.g002:**
[figure not shown]
A representative example of visual and linguistic information presented in each phase in the no priming condition.

Follow-up Control condition (*N* = 24): Although our pilot data (see below) suggest that 15-month-olds successfully establish novel object representations based on language input alone, it is important to rule out the possibility that their success is driven by the semantic relations among the objects themselves and therefore not dependent upon infants’ inferences about novel word meanings. We therefore plan a Follow-up Control condition, identical to the Semantic Priming condition with one exception: during Test, infants will hear a novel word that differs from that presented on Trial 4. If infants’ object preference at test is driven by the objects themselves, rather than naming, then performance in this Follow-up Control should not differ from that in the Semantic Priming condition. Conversely, if performance in the Semantic Priming condition is a consequence of verbal reference, then performance in this Follow-up Control condition should not differ from that in the No Priming condition.

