### Time course

We expect that the time course data will show significant divergences between the conditions after each verbal prompt. Based on our pilot data, we envision that after each prompt, infants in the Semantic Priming condition will exhibit increased proportion of looking to the target, which we predict to be above the chance level. In the Follow-up Control condition, infants’ looking behavior is likely to not be significantly affected by the verbal prompts because according to our hypothesis, they will have no particular expectations about the meaning of the novel word. It is, however, also possible that they will exhibit a weak preference for the target object (the object that is target in the Semantic Priming condition) based on their expectations about the next item shown given the relatedness of the three demonstrated objects. In the No Priming condition, infants have no basis to form any particular expectation about the object or the meaning of its label. For this reason, we expect that infants’ looking behavior will not be affects by the verbal prompts and remain around the chance level for the duration of the test trial.

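### The Follow-up Control is interpreted partly through 'no difference' statements that have no equivalence criterion, can hold together, and are not ranked against the predicted positive contrasts

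*Protocol article*

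**What the plan says.** The Follow-up Control repeats the Semantic Priming procedure but uses a different novel word at test. Its purpose is to separate inference about word meaning from relatedness of the objects.

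- Experiment 1, Procedure (Follow-up Control condition): if the objects drive the preference, "performance in this Follow-up Control should not differ from that in the Semantic Priming condition". If verbal reference drives it, "performance in this Follow-up Control condition should not differ from that in the No Priming condition".
- Predictions, Proportion of LT to the target: the first prediction is positive, with SP significantly above both NP and FC. The object-driven reading (FC no different from SP) is then repeated. For the word-meaning account the comparator changes from NP to 50%: "their LT in the Follow-up Control condition should not significantly deviate from chance". Of NP, looking to the two objects "will be equivalent and will not deviate significantly from chance".
- Time course: for FC, "It is, however, also possible that they will exhibit a weak preference for the target object", attributed to relatedness of the three objects shown.
- Participants: the sample size rests on the overall Condition F-test, with "power = .8, number of groups (experimental conditions) = 3, number of trials = 4, and projected correlation between measurements = .5" and f² = .1225 (f = .35). "Based on these parameters, the required number of participants is 72", that is 24 per condition.

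Experiment 2 reuses these analyses, and it goes ahead if Experiment 1 suggests success.

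**The concern.** A non-significant comparison of two groups of 24 does not show that they are equal. Here both explanations have a non-significant result as their expected signature, and the text presents them as converses. They are not complementary: an FC mean between SP and NP can be non-significant against both, and the data would then fit both accounts as written. The object-driven account has no positive test of its own. The word-meaning account has one (SP above FC), but the plan does not say that it overrides the null statements, and it gives that account two different null comparators (NP and chance). FC carries the paper's central claim, so an ambiguous reading there affects both the conclusion and the move to Experiment 2.

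**Working it through.** **1. The plan's sample size.** For a between-subject effect with m repeated measures, λ = f²·N·m / (1 + (m−1)ρ), with df (2, N−3).
- N = 72: λ = .1225 × 72 × 4 / 2.5 = 14.11, power .919.
- N = 54: λ = 10.58, power .814. N = 51 gives .789.

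The stated inputs therefore give 54 for 80% power, not 72. The larger number helps here and does not cause the problem. It was set for the overall Condition effect, not for any FC comparison.

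**2. The planning effect in points.** Assume SP stands apart from two equal conditions. The SD of three means, one of them shifted by Δ, is Δ√2/3, so Δ/σ = .35 × 3/√2 = .742 per trial. A mean of four trials with ρ = .5 has SD σ√(2.5/4) = .791σ, so d = .742/.791 = .939 on infant means.

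The pilot (Pilot data section) reports M 64%, SD 8% and t(17) = 5.5. These disagree: 14/(8/√18) = 7.42, while t = 5.5 implies SD = 14√18/5.5 = 10.8. Both SDs are carried forward. The planning effect is .939 × 8 = 7.5 points or .939 × 10.8 = 10.1 points.

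**3. SP versus FC with FC truly at chance.** Two-sided 5% t-test on infant means, 24 per group: noncentrality .939 × √12 = 3.25, power .89, so non-significant in about 11%. The result is the same at either SD, because d is fixed.

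**4. FC half-way.** d = .47, noncentrality 1.63, power .36, so each of SP-FC and FC-NP is non-significant in about 64%.

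**5. Joint outcomes** (simulation of normal infant means, n = 24 per group, NP at 50%; planning effect d = .939):

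| FC as a share of the SP effect | SP-FC n.s. | FC-NP n.s. | Both n.s. | FC vs 50% n.s. |
|---|---|---|---|---|
| 0 | 11% | 95% | 10% | 95% |
| 1/4 | 33% | 87% | 25% | 80% |
| 1/2 | 65% | 65% | 35% | 40% |
| 3/4 | 87% | 34% | 26% | 9% |
| 1 | 95% | 11% | 10% | 1% |

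**6. Full pilot effect** (SP 64, NP 50). With FC at 50 or 64, both nulls hold together in under 1% at either SD. With FC at 57 they do so in about 0.4% (SD 8) or 9% (SD 10.8).

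**7. What an equivalence test can do at n = 24.** At SD 8 the SE of a difference is 8√(2/24) = 2.31, and the 90% interval half-width is 1.679 × 2.31 = 3.88 points (5.23 at SD 10.8).
- A bound of ±7 points passes a truly zero difference in about 82% (SD 8) or 43% (SD 10.8). At SD 8 it also declares a half-way FC equivalent to SP in about 40% and to NP in about 39%, so it does not separate the accounts.
- A bound below half the planning effect (7.5/2 = 3.75 points) is narrower than the 3.88-point half-width. Simulated at ±3.5 points and SD 8, a truly zero difference passes in only about 1%.

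**The case against.** The strongest reply is that the plan already contains the right test. Its first prediction requires SP significantly above NP and FC, so if SP-FC is non-significant the word-meaning prediction has failed on the plan's own terms. This stands. A reader might infer that the control is read only through null results, and the document does not support that. What remains is that the object-driven account rests solely on a null and that no order of precedence is stated.

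The statements are also predictions of the form *if this account is true, expect that*. No sentence says that p > .05 establishes an account. That is fair, but they are the only stated guide to interpreting FC.

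Three further inferences are tempting and go too far:

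- *A true FC at chance would be taken as object-driven in about 35% of experiments.* That pairs a 7.5-point effect with SD 10.8. At the plan's f = .35 the effect at that SD is 10.1 points and the figure is 11%.
- *Missing a small FC preference reverses the conclusion.* With SP at 64 and FC at 53.5 (a quarter of the pilot effect), SP-FC is significant in 91–99% of experiments. The weak preference is also raised under Time course, which is the second outcome, not the 6-second average.
- *A different word might push FC below NP and be counted against verbal reference.* No passage predicts this, and it would widen the SP-FC contrast.

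Margins and contrasts may be left to a fuller analysis plan. Here, though, the article itself fixes the readings of FC, so their consistency can be judged from it.

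**Conclusion.** The concern holds in a limited form. The positive contrasts are correct, but the null statements beside them have no equivalence criterion, can be satisfied together and are not ranked against those contrasts. At the planning effect, a non-significant SP-FC result that the text would match to the object-driven account arises in about 11% of experiments when FC is truly at chance. FC differs from neither SP nor NP in about 10% when it sits at either extreme and in about 35% when it is half-way. If the full pilot effect is real and FC is at an extreme, the problem is negligible (under 1%).

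These figures assume 24 analysed infants per condition, normal infant means with equal SDs, NP at 50%, and pairwise t-tests standing in for the planned mixed model. The half-way position is an assumption; the document gives no size for the weak preference that it foresees.

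**What to change.** Before data collection, state in the Analyses and Predictions sections, for both experiments:

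1. The conclusion rests on the SP-NP and SP-FC contrasts from the mixed model, each with a 95% confidence interval. Abstract verbal reference is claimed only if both are significant in the predicted direction. Because both are required, alpha need not be split.
2. A non-significant SP-FC contrast is reported as *not resolved*, not as evidence that the objects drive the preference.
3. FC versus NP, and each condition against 50%, are supportive and reported as estimates with intervals.
4. Any claim of no difference or equivalence is made only through an equivalence test, with a bound fixed and justified beforehand and clearly smaller than half the planning effect.

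The change is to wording only, with no extra infants. The cost is that some experiments will end as not resolved: at the planning effect with FC at chance, both contrasts succeed in about 82% of simulated experiments, and with FC half-way in about 34%. With 24 per group, equivalence between conditions under so tight a bound would almost never be declared (step 7). The plan should say so and rely on the intervals, unless the sponsor chooses to enlarge the groups.
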